### 2.11. Statistical Analysis

All statistical analyses will be conducted using IBM SPSS Statistics, version 30.0.0, and R, version 4.5.0. The threshold for statistical significance will be set at α = 0.05. Two-tailed tests will be used unless a specific directional hypothesis is stated (e.g., the anticipated superiority of ETV over VPS), in which case one-tailed tests will be applied.

Continuous variables will first be tested for normality using the Kolmogorov–Smirnov test, and for homogeneity of variance using Levene’s test. If assumptions of normality and homoscedasticity are met, parametric tests such as the independent-samples *t*-test will be used. For repeated measures data, linear mixed-effects models will be applied instead of a traditional ANOVA to account for intra-subject variability and missing data points. If assumptions are violated, appropriate non-parametric alternatives (e.g., Mann–Whitney U test, Wilcoxon signed-rank test) will be applied.

To control Type I errors in multiple comparisons, a Bonferroni correction will be applied where appropriate. In addition to *p*-values, effect sizes (e.g., Cohen’s d for *t*-tests, η^2^ or partial η^2^ for ANOVA) will be reported to quantify the magnitude of observed effects.

For the analysis of longitudinal data, mixed-effects models will be used to account for intra-subject variability across follow-up points. These models will include fixed effects for time and the treatment group, as well as random intercepts to capture individual-level variability.

An a priori power analysis was performed assuming an effect size of Cohen’s d = 0.5, power (1 − β) of 0.80, and α = 0.05 (two-tailed). The estimated required sample size was 51 participants per group. This effect size was selected as a conservative estimate based on previously published studies evaluating pre- and postoperative cognitive and motor changes in patients with iNPH. Nonetheless, we recognize that this estimate may be optimistic. If the true effect is smaller, a larger sample size would be needed to retain adequate statistical power. This limitation is acknowledged, and future extensions of the study may involve adaptive or sequential design strategies to account for observed variability.

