The primary outcome will be the change in cognitive and motor performance over time. Cognitive functions will be evaluated using neuropsychological tests, focusing on memory, attention, executive function, and language. All cognitive assessments will be conducted both preoperatively and at each postoperative follow-up interval, as stated in the protocol. Motor outcomes will be assessed through gait analysis and coordination tests. All motor assessments will likewise be performed preoperatively and postoperatively using standardized tools including the Timed Up and Go (TUG) Test, the Baiobit wearable system, and the iNPH grading scale. The preliminary expectations are that patients in both the ETV and VPS groups will experience significant improvements in gait, as gait disturbance is typically the first symptom to improve following iNPH surgery. However, the degree of cognitive improvement may differ between the two groups, as prior evidence suggests that early intervention and reduced white matter compression may promote better cognitive recovery. By comparing cognitive trajectories in the ETV and VPS groups, this study aims to determine whether ETV has comparable or superior cognitive benefits relative to VPS. Structural changes in the brain will be analyzed using diffusion tensor imaging (DTI) and magnetic resonance imaging (MRI) with flowmetry. DTI will track changes in white matter integrity over the 12-month follow-up period. Since periventricular white matter is particularly vulnerable in iNPH, changes in the integrity of white matter tracts, such as the corticospinal tract, will be examined. The integrity of these tracts is essential for motor coordination and cognitive functions. Tractography will be used to visualize white matter pathways before and after surgery, providing insight into how ETV and VPS differentially affect white matter recovery. Neurophysiological changes will be measured using navigated transcranial magnetic stimulation (nTMS). This technique will allow researchers to assess motor cortical excitability and map changes in corticospinal tract connectivity. Motor evoked potentials (MEPs) will be recorded before surgery and at all follow-up intervals. An increase in MEP amplitude after surgery would suggest improved cortical excitability and the potential recovery of motor function. Differences in MEP amplitudes between the ETV and VPS groups may offer additional evidence regarding which procedure promotes superior motor recovery. Secondary outcomes will include the rate of complications, intensive care unit (ICU) stay, and patient-reported quality of life. Patients in the VPS group are expected to have a higher incidence of device-related complications, such as infection, shunt malfunction, and over-drainage, compared to the ETV group, which does not require the implantation of a foreign device. ICU stay and hospital length of stay will be compared between the two groups, with the hypothesis that ETV patients will have shorter stays due to the less invasive nature of the procedure. Quality-of-life measures will be obtained from patient self-reports, providing insight into the broader impact of surgery on daily living and well-being.

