
### Primary and Secondary Endpoints

This study’s primary outcome is the quantification of improvement in cognitive and motor performance from baseline to 12 months after VPS surgery or ETV. Secondary outcomes include the rate of postoperative complications (e.g., infection, device malfunction, or over-drainage), length of hospitalization, ICU stay, and patient-reported quality of life. To ensure that the study has sufficient power to detect meaningful differences between the two surgical groups, a power analysis was conducted. This analysis determined that a total sample size of 100 patients (50 in each group) would be required to achieve a power of 80% to detect an effect size (d) of 0.5 at a significance level of 0.05. The randomized controlled trial design, combined with standardized surgical protocols and the use of advanced neuroimaging and neurostimulation techniques, ensures that the results will be both statistically robust and clinically relevant.

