The methodological approach of this study is designed to overcome many of the limitations observed in previous research. By using a randomized controlled design with a sufficiently powered sample size of 100 patients (50 in the ETV group and 50 in the VPS group), this study will provide a statistically robust comparison of the two surgical techniques. The a priori power analysis assumed a medium effect size (Cohen’s d = 0.5), α = 0.05, and power of 80%. While this provides a practical sample estimate, we acknowledge that the true effect size may be smaller than anticipated, potentially requiring a larger cohort to maintain adequate statistical power. This limitation is recognized in the design and discussed transparently.

To ensure procedural consistency across participating institutions, all surgical teams will follow a shared and standardized operative protocol, developed collaboratively by the study investigators. Pre-trial workshops and training sessions will be organized to align technical approaches and perioperative care pathways. In addition, a central monitoring committee will oversee compliance with the protocol and conduct periodic audits to mitigate variability and ensure methodological integrity throughout the multicenter implementation.

In terms of radiological criteria, the diagnosis of iNPH and anatomical suitability for surgical procedures will also be based on the validated indices. In particular, the Evans index—defined as the ratio between the maximum width of the frontal horns and the inner diameter of the skull—will be used to confirm ventriculomegaly when greater than 0.3. Likewise, the callosal angle, measured in the coronal plane through the posterior commissure, provides additional diagnostic confidence, with angles below 90° typically associated with iNPH.

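### The stated basis for d = 0.5, studies of pre- to postoperative change, does not support it as a between-arm effect, and at that d the trial has 69.7% two-sided power, not 80%

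*Protocol article*

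**What the plan says.** Section 2.11 sets the inputs: "An a priori power analysis was performed assuming an effect size of Cohen’s d = 0.5", with two-tailed α = 0.05 and power 0.80. It adds: "The estimated required sample size was 51 participants per group". The basis for d is given as: "This effect size was selected as a conservative estimate based on previously published studies evaluating pre- and postoperative cognitive and motor changes in patients with" the disease. The next sentence concedes that the figure could be too favourable, and the paragraph accepts that a smaller true effect would call for more patients.

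The section Primary and Secondary Endpoints says the calculation is meant to detect a difference between the arms, and that 100 patients, 50 per group, "would be required to achieve a power of 80% to detect an effect size (d) of 0.5 at a significance level of 0.05". The primary outcome there is improvement from baseline to 12 months.

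Section 3 expects that "patients in both the ETV and VPS groups will experience significant improvements in gait". The Introduction describes both procedures as effective, and the Discussion hypothesises that ETV will do at least as well as VPS. The Discussion also introduces the design with: "By using a randomized controlled design with a sufficiently powered sample size of 100 patients". It calls d = 0.5 a medium effect and repeats the caveat that the truth may be smaller.

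**The concern.** For a two-arm comparison of 12-month improvement, d is the ETV minus VPS difference in mean change divided by the SD of change. Studies of pre- and postoperative change describe how far operated patients move from their own baseline. When both arms are active and both are expected to improve, the between-arm effect is the difference of two such changes, and the size of one does not determine it. The article gives no comparative source, no expected ETV minus VPS difference and no SD of change.

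The label *conservative* therefore has no support on the stated basis. At stake is how a non-significant result is read. Someone who relies on the 80% and on the Discussion's claim of adequate size may take it as evidence that the operations perform alike, when the trial may simply be imprecise.

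**Working it through.** **Inputs.** d = 0.5, two-sided α = 0.05, power 0.80 and 51 per group (Section 2.11); 50 per group (Primary and Secondary Endpoints); 1:1 allocation (Section 2). No dropout figure is given, so the results below assume complete data.

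**1. Reproducing the stated sample size.** Normal approximation, n per arm = 2(z₁ + z₂)²/d²:

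- Two-sided: 2(1.960 + 0.842)²/0.25 = 62.8, so 63. Noncentral t: 63.8, so 64.
- One-sided: 2(1.645 + 0.842)²/0.25 = 49.5, so 50. Noncentral t: 50.2, so 51.

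The article's 50 and 51 come out only with a one-sided test. Section 2.11 states two-tailed for this calculation, although it allows that for a directional hypothesis there is a setting "in which case one-tailed tests will be applied".

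**2. Power at the stated d.** With n = 50 the noncentrality is d√(n/2) = 0.5 × √25 = 2.5. Normal approximation, two-sided: Φ(2.5 − 1.960) = 70.5%. Noncentral t (98 df): 69.7% two-sided, 79.9% one-sided. With 51 per arm: 70.6% and 80.6%. The smallest d with 80% two-sided power at 50 per arm is 0.566, or about 0.57.

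**3. Power at 50 per arm for other between-arm values (t-test, α = 0.05).**

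| Between-arm d | Two-sided | One-sided | n per arm for 80%, two-sided |
|---|---|---|---|
| 0.5 | 69.7% | 79.9% | 64 |
| 0.4 | 50.8% | 63.4% | 100 |
| 0.3 | 31.8% | 43.8% | 176 |
| 0.25 | 23.6% | 34.3% | 253 |

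**4. What a pre-post effect implies for the between-arm d.** Assume both arms share one SD of change and all effects are standardised by it. If VPS has pre-post effect w and ETV improves f times as much, then between-arm d = (f − 1)w. The documents give neither w nor f, so both are assumptions:

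| w (VPS) | f = 1.25 | f = 1.5 | f = 2 |
|---|---|---|---|
| 0.5 | 0.125 (9.5%) | 0.25 (23.6%) | 0.5 (69.7%) |
| 0.8 | 0.20 (16.8%) | 0.40 (50.8%) | 0.80 (97.7%) |
| 1.0 | 0.25 (23.6%) | 0.50 (69.7%) | 1.0 (99.9%) |

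Brackets show two-sided power at 50 per arm. If w = 0.5, ETV would have to double the VPS gain (or, in the other direction, achieve none) to reach 0.5. If w = 1.0, a gain half as large again is enough. The pre-post evidence alone therefore does not fix the between-arm d.

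**The case against.** Five points count on the other side.

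- *The sources are not shown.* Being based on studies of pre- and postoperative change does not make 0.5 a within-patient d. It may have been scaled down from larger observed changes, or picked as a conventional medium effect, as the Discussion's wording suggests. This stands: the defect is in the stated justification, and 0.5 is not shown to be numerically wrong.
- *Power is conditional on d.* A reader might infer that the 80% fails because of where 0.5 came from. It does not: power at a between-arm d of 0.5 is the same whatever motivated that value. The 80% fails because 50 or 51 per arm matches a one-sided test.
- *The low figures depend on the inputs.* A reader might infer that the real power is about 24% or less. The second table shows that this needs particular combinations of w and f, and others reach 0.5 or more.
- *A difference in cognition is anticipated.* Section 3 allows that cognitive gains may differ between arms, and Section 4.1 describes cognitive recovery after ETV as slower and harder to predict. So the article does not itself predict a negligible difference on the whole primary outcome.
- *The limitation is disclosed.* Section 2.11 and the Discussion both concede that the true effect may be smaller. This softens the point. It does not cure it, because neither place recognises that change from baseline and a difference between arms are separate quantities, and the Discussion keeps its claim of adequate size.

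**Conclusion.** The point holds as a defect in justification and in a stated property of the design. The basis given in Section 2.11 does not support a between-arm d of 0.5, and *conservative* conflicts with the sentence after it. The documents do not support going further, to say that 0.5 is wrong or that power is some specific low figure. The implied between-arm d runs from 0.125 to 1.0 over the assumed inputs tabulated, all under a common SD of change.

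What can be stated firmly is conditional on d. With 50 per arm, complete data and a two-sided 0.05 t-test, power at 0.5 is 69.7%, about 10 percentage points below the stated 80%. That shortfall is a matter of sidedness and sample size, separate from the source of d; raising the sample to 64 per arm would remove it and still leave 0.5 without a between-arm rationale.

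**What to change.** 1. **Section 2.11.** Delete *conservative* and the reference to pre-post studies. Present d = 0.5 as a chosen target for the ETV minus VPS difference in 12-month change. Bring the sentence on required sample size into line with the two-tailed test.
2. **Primary and Secondary Endpoints, and Discussion.** Replace the 80% statement and the claim of adequate size with what 50 per arm delivers at two-sided 0.05: 69.7% power at d = 0.5, 80% only at d = 0.57, and 51%, 32% and 24% at d = 0.4, 0.3 and 0.25.
3. **Optional.** Report the 12-month between-arm estimate with its 95% confidence interval as the main result, so that a non-significant finding is read as imprecise. This suits the Abstract's description of an initial study that will inform larger trials.

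The cost is wording only, with no added patients or procedures. The one downside is that the stated power looks less favourable.

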## 3. Expected Results

The results of this study will offer valuable insights into the comparative effectiveness of ETV and VPS in treating patients with iNPH. Cognitive, motor, and structural changes will be analyzed at the preoperative baseline and at 1 week, 3 months, 6 months, and 12 months post-surgery. Data will be collected from 100 patients who will be randomly assigned to either the ETV or VPS group. The analysis will focus on how each surgical approach influences cognitive recovery, gait improvements, and white matter integrity.

The primary outcome will be the change in cognitive and motor performance over time. Cognitive functions will be evaluated using neuropsychological tests, focusing on memory, attention, executive function, and language. All cognitive assessments will be conducted both preoperatively and at each postoperative follow-up interval, as stated in the protocol. Motor outcomes will be assessed through gait analysis and coordination tests. All motor assessments will likewise be performed preoperatively and postoperatively using standardized tools including the Timed Up and Go (TUG) Test, the Baiobit wearable system, and the iNPH grading scale. The preliminary expectations are that patients in both the ETV and VPS groups will experience significant improvements in gait, as gait disturbance is typically the first symptom to improve following iNPH surgery. However, the degree of cognitive improvement may differ between the two groups, as prior evidence suggests that early intervention and reduced white matter compression may promote better cognitive recovery. By comparing cognitive trajectories in the ETV and VPS groups, this study aims to determine whether ETV has comparable or superior cognitive benefits relative to VPS. Structural changes in the brain will be analyzed using diffusion tensor imaging (DTI) and magnetic resonance imaging (MRI) with flowmetry. DTI will track changes in white matter integrity over the 12-month follow-up period. Since periventricular white matter is particularly vulnerable in iNPH, changes in the integrity of white matter tracts, such as the corticospinal tract, will be examined. The integrity of these tracts is essential for motor coordination and cognitive functions. Tractography will be used to visualize white matter pathways before and after surgery, providing insight into how ETV and VPS differentially affect white matter recovery. Neurophysiological changes will be measured using navigated transcranial magnetic stimulation (nTMS). This technique will allow researchers to assess motor cortical excitability and map changes in corticospinal tract connectivity. Motor evoked potentials (MEPs) will be recorded before surgery and at all follow-up intervals. An increase in MEP amplitude after surgery would suggest improved cortical excitability and the potential recovery of motor function. Differences in MEP amplitudes between the ETV and VPS groups may offer additional evidence regarding which procedure promotes superior motor recovery. Secondary outcomes will include the rate of complications, intensive care unit (ICU) stay, and patient-reported quality of life. Patients in the VPS group are expected to have a higher incidence of device-related complications, such as infection, shunt malfunction, and over-drainage, compared to the ETV group, which does not require the implantation of a foreign device. ICU stay and hospital length of stay will be compared between the two groups, with the hypothesis that ETV patients will have shorter stays due to the less invasive nature of the procedure. Quality-of-life measures will be obtained from patient self-reports, providing insight into the broader impact of surgery on daily living and well-being.

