### 2.10. Postoperative Evaluation

The postoperative follow-up protocol is designed to evaluate recovery and assess the efficacy of the surgical interventions. Follow-ups will occur at 1 week, 3 months, 6 months, and 12 months after surgery. During these evaluations, cognitive and motor assessments will be repeated, and imaging studies will track the structural changes in white matter and ventricular size. At the follow-up times, patients will undergo repeated neuropsychological and motor performance evaluations using the same tools administered preoperatively. This will enable a direct comparison of cognitive and motor recovery over time [4,12]. MRI with flowmetry and DTI will be performed during each follow-up to monitor changes in ventricular size, CSF flow, and white matter integrity. These imaging modalities provide critical insights into the structural effects of ETV and VPS on the brain [11,12]. At the same follow-up, nTMS will assess postoperative changes in corticospinal excitability and motor pathway recovery. Changes in MEPs will serve as objective indicators of neuroplasticity and functional improvement. Additionally, repetitive TMS (rTMS) may be explored as a therapeutic tool to further enhance motor recovery [12]. This integrated approach ensures a thorough evaluation of the effects of ETV and VPS on iNPH patients, providing a robust dataset to inform clinical decision making and improve treatment outcomes.

Quality of life will also be systematically assessed using the SF-36 Health Survey, a validated instrument capturing both physical and mental health domains from the patient’s perspective. This tool will be administered preoperatively and at each follow-up interval to longitudinally evaluate patient-reported outcomes.

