### 4.1. VPS Versus ETV: Pros and Cons

The surgical treatment of iNPH is centered around two main approaches: endoscopic third ventriculostomy (ETV) and ventriculoperitoneal shunt (VPS) [9]. Each of these procedures offers distinct benefits and limitations, making the choice of treatment highly dependent on patient-specific factors, anatomical characteristics, and clinical goals. One of the key advantages of ETV is the elimination of the need for an implantable device [41]. Unlike VPS, which relies on a catheter and valve system to drain cerebrospinal fluid (CSF) from the brain to the peritoneal cavity, ETV creates a natural internal pathway for CSF flow. This approach avoids the risk of mechanical failure, disconnection, and infection associated with implanted devices. By removing the dependency on an external device, ETV reduces the overall burden on healthcare systems, as it does not require lifelong device monitoring or replacement surgeries. Another important advantage of ETV is the reduced risk of postoperative infection. Since no foreign object is implanted, the likelihood of infection is significantly lower compared to VPS, where the presence of an implanted shunt system increases susceptibility to bacterial colonization. ETV also provides a long-term solution for many patients, as it re-establishes the body’s natural CSF flow dynamics, thereby reducing the need for future surgical revisions [42,43]. Unlike VPS, where shunt failure often necessitates additional surgeries, ETV patients are less likely to require repeat procedures. Additionally, the absence of complications related to over-drainage, which is a known risk of VPS, further highlights the stability and sustainability of ETV. Over-drainage, often seen in VPS patients, can result in subdural hematomas, but this risk is inherently avoided in ETV due to its reliance on natural flow mechanisms. Moreover, ETV has been associated with shorter hospital stays, fewer intensive care unit (ICU) admissions, and faster recovery times. Given the minimally invasive nature of the procedure, patients often experience less postoperative discomfort and a quicker return to daily activities compared to those who undergo VPS. Despite these advantages, ETV also has certain limitations that must be considered when selecting a treatment for iNPH. A critical disadvantage of ETV is its dependence on patient-specific anatomical factors [9]. The procedure requires sufficient anatomical space within the third ventricle and basal cisterns to safely create a new pathway for CSF flow. In patients with anatomical anomalies, such as a narrow or distorted third ventricle floor, ETV may be technically infeasible. Furthermore, ETV is a more technically demanding procedure that requires specialized neurosurgical skills and advanced neuronavigation technology. The surgeon must ensure that the perforation of the third ventricle floor does not damage critical adjacent structures, such as the basilar artery, as such damage could lead to severe complications, including stroke. Another significant challenge with ETV is the risk of stoma closure. Over time, the opening created in the third ventricle may close due to scarring or the accumulation of cellular debris, thereby blocking the CSF flow and necessitating additional surgical intervention. Unlike VPS, which allows for shunt adjustments, ETV does not offer a means for mechanical control or adjustment after the surgery is complete. Additionally, while ETV is generally effective for resolving gait disturbances, the evidence regarding its impact on cognitive recovery is mixed. Cognitive improvements after ETV are often slower and less predictable, as cognitive recovery depends on the restoration of periventricular white matter pathways. Delayed cognitive recovery may be attributed to the slow process of white matter reorganization following the release of ventricular compression. From a patient-centered perspective, ETV would provide a better quality of life, as it would eliminate the need for a permanent shunt and reduce the risk of repeated surgical interventions. This outcome would also have economic benefits, as VPS requires frequent monitoring, shunt revisions, and hospitalization for complications, whereas ETV offers a more definitive, one-time solution.

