
On the other hand, VPS offers a different set of benefits that make it a widely used approach for the treatment of iNPH. One of its most notable advantages is its applicability to a broader range of patients [9,41,42,43,44]. Unlike ETV, which requires a specific anatomical configuration to be effective, VPS can be used in almost all patients with iNPH, regardless of their ventricular anatomy. This versatility allows neurosurgeons to treat patients who would otherwise be ineligible for ETV due to unfavorable anatomical features, such as narrow ventricles or the presence of subarachnoid scarring. VPS also provides a more predictable and immediate resolution of symptoms. Many patients experience an almost immediate improvement in gait, balance, and motor coordination following the procedure [9,41,42,43,44,45]. This immediate symptom relief can have a profound impact on patient quality of life, especially in those with severe gait impairments. The procedure is well-documented, and its effectiveness has been established through decades of clinical practice and research. Neurosurgeons are highly familiar with VPS procedures, and well-established surgical protocols ensure a high degree of predictability in outcomes. This predictability extends to the management of complications as well. Since VPS systems are widely used, shunt components, valves, and catheters are readily available, and the replacement of faulty or malfunctioning components is straightforward. The design of modern shunt systems, which often includes programmable valves, allows neurosurgeons to adjust the flow rate of CSF drainage as needed, offering greater control over the treatment process. Nevertheless, VPS is not without its drawbacks. One of the most significant disadvantages of VPS is the patient’s lifelong dependence on an implanted device. Once the shunt is placed, the patient becomes reliant on its continued functionality to maintain normal CSF dynamics. If the shunt fails—due to a blockage, disconnection, or mechanical malfunction—the patient may experience a rapid return of iNPH symptoms, such as gait instability and cognitive decline, necessitating immediate medical attention. The risk of shunt failure is substantial, with studies reporting that up to 40% of VPS patients require at least one shunt revision during their lifetime [9,41,42,43,44,45,46]. Revision surgeries are costly, invasive, and increase the patient’s risk of infection, anesthesia-related complications, and further surgical trauma. Infection is another critical concern with VPS, as the introduction of a foreign device into the body creates an opportunity for bacterial colonization. Shunt infections can be difficult to treat, often requiring removal of the device, intravenous antibiotic therapy, and subsequent re-implantation. In some cases, infection-related complications result in prolonged hospital stays and increased healthcare costs. VPS also carries a risk of over-drainage, which occurs when too much CSF is drained from the brain’s ventricles, resulting in subdural hematomas. This complication is particularly concerning for elderly patients, whose brains are more susceptible to the effects of over-drainage due to brain atrophy. Over-drainage can result in significant neurological deficits and may necessitate emergency intervention. Additionally, VPS patients require long-term follow-up to monitor shunt function and detect potential malfunctions. Unlike ETV, which is often a “one-and-done” procedure, VPS requires continuous oversight and lifetime device monitoring [9,41,42,43,44,45,46]. These follow-ups place a financial and logistical burden on both patients and healthcare systems, as they involve regular check-ups, radiological evaluations, and emergency revisions when problems arise.

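### The primary outcome is stated both as change over time and as change to 12 months, and the mixed model's group effect averages the visits, so it is not the 12-month difference

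*Protocol article*

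**What the plan says.** The protocol article states the primary outcome twice.

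- **Section 3, Expected Results:** "The primary outcome will be the change in cognitive and motor performance over time". No visit is named. The same section says that cognitive trajectories in the two arms will be compared, and that "changes will be analyzed at the preoperative baseline and at 1 week, 3 months, 6 months, and 12 months post-surgery".
- **Primary and Secondary Endpoints:** the outcome is the "quantification of improvement in cognitive and motor performance from baseline to 12 months after VPS surgery or ETV".

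Section 2.10 gives the schedule: "Follow-ups will occur at 1 week, 3 months, 6 months, and 12 months after surgery".

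Section 2.11 offers an independent-samples t-test (or a non-parametric alternative) and, for repeated measures, a linear mixed-effects model. The model's stated fixed effects are time and treatment group, with random intercepts; no group-by-time term is named. Bonferroni correction is to be used where appropriate. The section does not say which analysis or contrast carries the primary comparison.

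Section 4.1 comments on timing. Of the shunt it says "VPS also provides a more predictable and immediate resolution of symptoms". Of the endoscopic procedure it says "Cognitive improvements after ETV are often slower and less predictable". It also associates ETV with faster recovery and an earlier return to daily life, and warns that the stoma may close later.

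**The concern.** Change over time, compared as a trajectory, and change from baseline to 12 months are different targets. The first can mean an average or a profile over four postoperative visits. The second is one difference at one visit. They coincide only if the treatment difference is the same at every visit.

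The analysis section does not settle the matter. In a model with time and group as main effects and no interaction, the group coefficient is a single number, assumed common to all visits and estimated from all of them. It gives 1 week a say equal to 12 months when data are complete. A team that follows Section 2.11 as written would therefore test something other than the outcome in the endpoints section. A t-test on 12-month change would match that outcome. Both routes are open.

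At stake is which result is reported as primary. If the treatment difference changes during follow-up, the two contrasts can lead to different conclusions from the same data. If the choice is made after the data are seen, the error rate per score exceeds the stated 5%.

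**Working it through.** **Inputs from the protocol article.** 50 patients per arm (Primary and Secondary Endpoints); four postoperative visits (Section 2.10); α = 0.05, two-tailed, and d = 0.5 (Section 2.11).

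**Assumptions, since the article gives no figures.** Each visit's change score has SD 1. Any two visits have the same correlation ρ, taken as 0.3, 0.5 and 0.7. Data are complete. Effects are in SD units, ETV minus VPS, with positive values favouring ETV. The article states no power or error figure for a choice between contrasts, so there is none to reproduce.

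**Step 1. The two contrasts.**

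- 12 months: the effect is δ₁₂, with standard error √(2/50) = 0.20.
- Visit average: the effect is the mean of the four visit effects. The SD of a patient's average is √((1 + 3ρ)/4), which is 0.689, 0.791 and 0.880 for ρ = 0.3, 0.5 and 0.7. The standardised effect is the mean effect divided by that SD.
- Power is that of the two-sided two-sample t-test with 98 degrees of freedom and noncentrality equal to the standardised effect × √(50/2), that is, × 5.

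**Step 2. An early VPS lead that closes: −0.5, −0.25, −0.1, 0.** The mean is −0.85/4 = −0.2125.

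| ρ | Standardised average | Noncentrality | Power, average | Rejection rate, 12 months |
|---|---|---|---|---|
| 0.3 | −0.308 | −1.54 | 33% | 5% |
| 0.5 | −0.269 | −1.34 | 27% (26.5%) | 5% |
| 0.7 | −0.241 | −1.21 | 22% | 5% |

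Rejections by the average favour VPS. At 12 months the true difference is zero, so the 5% is the false-positive rate. The two definitions answer differently here without any late ETV advantage being assumed.

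**Step 3. A constant effect of 0.5 at every visit.** The mean is 0.5.

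| ρ | Standardised average | Noncentrality | Power, average | Power, 12 months |
|---|---|---|---|---|
| 0.3 | 0.725 | 3.63 | 95% | 70% |
| 0.5 | 0.632 | 3.16 | 88% | 70% |
| 0.7 | 0.568 | 2.84 | 80% | 70% |

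Here averaging is the more powerful choice, and the direction is the same.

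**Step 4. Error if either contrast may be called primary.** Under no difference at any visit, the two test statistics have correlation √((1 + 3ρ)/4), that is 0.689, 0.791 and 0.880. The probability that at least one exceeds 1.96 in absolute value, by simulation with 1,000,000 draws, is 8.4%, 7.9% and 7.2% for ρ = 0.3, 0.5 and 0.7. This applies to one score; several cognitive and motor scores would add to it.

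**The case against.** The strongest reply is that this is loose wording rather than two rival endpoints. The endpoints section is the place to look, it names 12 months, and the Section 3 phrase can be read as change over the 12-month follow-up. An article also condenses, and the model's full specification may sit in an analysis plan that is not shown. Much of this stands: the 12-month reading is the natural one, and the conflict is an ambiguity to reconcile. It does not remove the point. Section 3 goes on to compare trajectories, and Section 2.11 states a set of fixed effects whose group term is not the 12-month difference. An analysis plan written from this text would inherit both.

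Two stronger readings are tempting but unsupported.

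- **That the protocol expects early visits to favour VPS and late visits to favour ETV.** No section predicts better late cognitive or motor scores after ETV. The late arguments for ETV in Section 4.1 concern devices, infection and revisions, and possible stoma closure points the other way. Even the early direction is mixed, since the same section credits ETV with faster recovery. The hypothesis in the Discussion, comparable or superior outcomes, names no visit.
- **That any of the four visits could be claimed as primary.** Four unadjusted tests at 0.05 would give an error of 15.6% at ρ = 0.5. Listing visits for analysis does not make each one a primary test, and Section 2.11 describes a mixed model and a Bonferroni correction, not that procedure. The choice actually left open is visit average against 12 months.

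It is also fair to object that the power figures depend on the effect pattern chosen. They do, and Step 3 shows a pattern in which averaging does better.

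**Conclusion.** The point holds as an inconsistency that should be reconciled. The primary outcome is worded two ways in time, and the model as stated yields a visit-averaged group effect that is not the 12-month difference of the endpoints section. Section 4.1 gives reason to think that the treatment difference may change between visits, which is when the two contrasts part.

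The size is moderate. An unfixed choice between the two contrasts puts the two-sided error at about 7% to 8% per score instead of 5%. Power ranges from 22% to 33% in favour of VPS for the average against 5% at 12 months, if an early VPS lead closes, to 80% to 95% against 70%, if the effect is a constant 0.5 SD. These figures rest on assumed effects, equal correlations of 0.3 to 0.7 and complete data. They show that the choice can matter, not that it will reverse the trial's conclusion.

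**What to change.** Three changes to the text:

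1. In Section 3, replace the open wording with the 12-month time point already used under Primary and Secondary Endpoints.
2. In Section 2.11, state that the primary contrast for each primary score is the between-arm difference in change from baseline to 12 months, estimated from a mixed model with visit as a category and a group-by-visit term.
3. Label the differences at 1 week, 3 months and 6 months, and the trajectory comparison, as supportive, reported with confidence intervals.

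This fixes the time point and contrast for each score. It does not reduce the primary analysis to one test, because the outcome still spans several cognitive and motor scores.

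No further patients, visits or data are needed. The cost is that an early or visit-averaged difference can no longer be claimed as the primary result. If the effect is in fact constant over visits, the 12-month contrast also has less power than averaging: 70% against 80% to 95% in Step 3.
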